### Monitoring

The exercise intervention is low risk and is commonly used in the population. The occurrence of an adverse event as a result of participation within this study is not expected, and no adverse event data will be collected.

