### Purpose

The primary aim is to establish the feasibility and acceptability of conducting a definitive RCT which will evaluate the clinical and cost-effectiveness of a loaded self-managed exercise programme for people with patellofemoral pain compared to usual physiotherapy.

Secondary aims include establishing: if the devised loaded self-managed exercise programme can be delivered as planned in an NHS physiotherapy outpatient clinic; if the outcome measures are feasible to use within an NHS setting; if reliable data can be collected; a sample size calculation for an RCT; if the intervention is acceptable and tolerable to participants and physiotherapists; if it is feasible to recruit and randomise participants; the potential barriers to recruitment and the training package delivered to physiotherapists.

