#### Phase 2 —pilot clinical trial

##### Exercise intervention

The ‘experimental’ intervention is a loaded self-managed exercise programme for the knee and hip, aimed at addressing lower limb knee and hip weakness [25]. It is set within a framework of reducing fear/avoidance and with an emphasis on self-management and reducing the need for direct physiotherapy intervention.

Before any prescription of exercise, the physiotherapist will spend a period of time educating the participant about pain mechanisms. Descriptions of tissue-based pathology models of pain, e.g. patellar mal-tracking, or limb mal-alignment, will be actively discouraged and challenged by the physiotherapist. The participant will gain an evidence-based understanding of dysfunctional central nociceptive processing as an explanation of chronic and persistent pain [42] and the role and impact of fear [43]. This period of intense learning is designed to facilitate the reconceptualisation of pain, with an emphasis on descriptions of pain neuroscience rather than psychology [44], and from the perspective and context of the participant and their pain [45]. The education regarding pain mechanisms will take up a large portion of clinical time, such as to address any beliefs or fear within the participant that pain is a sign of tissue damage, and will be delivered in a Socratic teaching style [46]. It is expected that the education period will be completed in the first session, which typically lasts 30–40 min within the NHS, but participants that require further re-assurance may continue into their second session.

The exercise will be prescribed by the physiotherapist and will typically involve body weight resistance in the form of a modification of the ‘Step Down’ function test [47], a single-leg squatting exercise sideways on a step. By performing sideways, the participant will be able to use the guide of the wall and/or banister more easily, as guided by our patient and public involvement feedback. The exercise requires balance, knee extension strength, eccentric control and isometric hip strength. The participant will be advised to exercise to the point of fatigue, such that it reproduces their pain and discomfort, but ensuring the pain is manageable [48–50].

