Exercise progression is guided by symptomatic response, such that the participant is advised that on cessation of the exercise, the pain should remain no worse than pre-exercise [48]. Participants with more severe pain will start on a lighter regime, and this will be guided by the baseline functional assessment by the treating physiotherapist. Participants will be advised to exercise at a level they find acceptable and tolerable. Participants are able to start exercising, if they wish, at a very low level, with little or no short-term pain increase, and progress when they feel comfortable and confident. Regression will be in the form of reduced repetitions, or lightening the exercise, for example to double leg squats 0–30° knee flexion. Progression can be in the form of increased repetitions or increasing the load by moving to plyometric exercises, such as jumping and hopping, for participants with higher sporting requirements. The physiotherapist will plan the exercise, motivate and review participant’s physical performance and expectations [35].

A single exercise approach will be used for this intervention. Poor levels of exercise adherence are well documented [51], and it has been suggested that a single exercise represents a pragmatic time saving approach [52]. Additionally, as previously discussed, the optimal dosage of an exercise prescription is unknown, and a single exercise approach may allow better monitoring of dosage and adherence. Importantly, it will enable the participant to observe others (the physiotherapist) perform the task successfully, and facilitate the development of mastery of the task. This combined with specific verbal and social persuasion from the physiotherapist, will further promote reconceptualisation of the pain, specific to the participant and their context; all thought to be key modifiers of perceived self-efficacy [53].

The participants will be advised that the exercise should be performed twice a day. The participant will be encouraged to self-direct in progressing/regressing the repetitions, as guided by their pain response, thus further internalising the locus of control and moving towards self-management [53].

Goal setting will be a central part of the intervention. The reconceptualisation of pain through the exercise intervention leads to the reconceptualization of pain in the participant’s daily activities, including sport and leisure activity, and setting goals helps this transition.

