### Planned data analysis

#### Phases 1 and 3

The qualitative components will follow a thematic analysis approach, as described by Braun and Clarke (2006) [73]. Line by line coding, leading to a thematic analysis (using an abductive research strategy), will be used. Following data familiarisation, initial codes will be generated and peer reviewed, by a member of the research group, to search for common themes. This will be carried out using the NVivo software (NVivo qualitative data analysis Software; QSR International Pty Ltd., Version 11, 2015). For phase 1, the analysis will assess the lived experience of PFP; for phase 3, the analysis will broadly assess acceptability and feasibility of study design, intervention and training package to physiotherapists.

#### Phase 2

The analysis will focus on descriptive statistics and confidence intervals for the variables we are obtaining. The characteristics of the participants will also be described using means, standard deviations and ranges for quantitative variables and counts and proportions for categorical variables.

As this is a feasibility study, we are testing our ability to collect data; therefore, no data imputation will be performed to account for any missing data.

Feasibility threshold will be set at 75% for recruitment. Feasibility threshold will be set at 75% to assess reliability and completeness of outcome measures. Data relating to timing of the return of outcome forms, department referral rate, recruitment rate and numbers lost to follow-up will be recorded. Acceptability and tolerability of the treatment intervention will be assessed through completeness of outcome measures and feedback from the phase 3 qualitative interviews.

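### No adverse event data will be collected, so adverse events cannot be counted, compared between arms or reported, although tolerability is an aim

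*Protocol article*

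**What the plan says.** - **Monitoring** gives the reason and the rule. The reason is that "The exercise intervention is low risk and is commonly used in the population". The rule is that an adverse event arising from participation "is not expected, and no adverse event data will be collected".
- **Purpose** lists among the secondary aims to establish "if the intervention is acceptable and tolerable to participants and physiotherapists".
- **Planned data analysis, Phase 2** says how that aim is to be met: "Acceptability and tolerability of the treatment intervention will be assessed through completeness of outcome measures and feedback from the phase 3 qualitative interviews".
- **Exercise intervention** (Phase 2) has participants "advised to exercise to the point of fatigue, such that it reproduces their pain and discomfort, but ensuring the pain is manageable". Progression can include "increasing the load by moving to plyometric exercises, such as jumping and hopping, for participants with higher sporting requirements". The same section allows a low-level start with little added pain, says that pain after stopping should be no worse than before, and plans a discussion of how to manage flare-ups.
- **Phase 3 interviews** sample eight to ten participants from both arms together, starting 6 months after randomisation.

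**The concern.** The decision to record nothing rests on the expectation that nothing will happen. That expectation is an assumption about a programme the protocol itself calls experimental, which is largely self-managed and for which the best dose is described as unknown. A feasibility trial is the natural place to test such an assumption. If no event is recorded, the assumption can be neither confirmed nor contradicted.

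The rule also sits awkwardly with the tolerability aim. Completeness of outcome measures shows whether forms came back filled in. A participant who was injured, fell, or stopped exercising because of a flare can still return a complete form, and one with no problem at all may fail to return it.

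The definitive trial is at stake. It would be planned without an adverse event rate in either arm and without a tried way of recording events. Events not recorded during the trial cannot be reliably recovered afterwards.

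**Working it through.** The protocol gives no figure on this point to reproduce. The check has two parts.

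**1. Do the data that are collected stand in for adverse events?**

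| Source (section) | What it can show | What it cannot show |
|---|---|---|
| Pain VAS (Outcome assessments) | Average pain over the past week, at 3 and 6 months | Injury, falls, or a flare between those points; cause |
| 7-point global rating (Outcome assessments) | Worsening, at the bottom of the scale | Cause; the primary outcome reduces it to recovered or not |
| EQ-5D-5L (Outcome assessments) | General health, including pain, at follow-up | Discrete events; cause |
| Exercise diary (Outcome assessments) | Repetitions, so possibly when exercise stopped | Why it stopped; no symptom or event entry is described |
| Numbers lost to follow-up (Planned data analysis) | Attrition | Whether harm was the reason |
| Phase 3 interviews | Individual accounts, including from non-responders | A rate, or a comparison between arms, from eight to ten people |

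These give indirect signals of worsening. None gives a count of adverse events by arm.

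**2. What would collection give at this sample size?**

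Inputs: 30 per arm (Sample size). The completeness threshold is 75% (Planned data analysis); 0.75 × 30 = 22.5, so 22 or 23 reporting. The true event rates below are assumptions, because the protocol states none.

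*Upper limit if no event is seen*, exact two-sided 95%: 1 − 0.025^(1/n).
- n = 30: 1 − 0.025^(1/30) = 11.6%
- n = 23: 1 − 0.025^(1/23) = 14.8%
- n = 22: 1 − 0.025^(1/22) = 15.4%

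*Chance of seeing at least one event in an arm of 30*: 1 − (1 − p)^30.
- p = 1%: 26%
- p = 2%: 45%
- p = 5%: 79%
- p = 10%: 96%

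With 22 or 23 reporting and p = 5%, the chance is 68% or 69%.

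*Precision if events do occur*: 3 events in 30 (10%) would have an exact 95% interval of 2.1% to 26.5%.

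The information would be coarse and descriptive, but useful for planning. Under the present rule none of these quantities can be computed.

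**The case against.** The strongest defence is that the decision is deliberate and reasoned. The exercise is described as low risk and in common use, the primary aim is feasibility and acceptability, and randomisation, the primary outcome and the feasibility thresholds are untouched. The risk is also hedged: pain must be manageable, a near pain-free start is allowed, and jumping and hopping are only for those with higher sporting requirements. The protocol treats flare-ups as a self-management topic and does not class them as adverse events. All of this is correct, and it limits how strongly the point can be put. It does not allow the expectation of no events to be checked.

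A reader might infer that the trial can say nothing about harm, or that the tolerability aim cannot be answered at all. The document does not support either. Pain, global rating and EQ-5D-5L are collected at both follow-ups, so worsening by arm is partly visible. A method for assessing tolerability is stated, and the interviews seek out non-responders and participants lost to follow-up. That method is weak for this purpose, but it exists.

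It could also be said that a journal article leaves such detail to the full protocol. That does not help here, because the article states a decision not to collect.

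A last objection concerns the remedy. Recording events at treatment sessions would not be even-handed. Session numbers are discretionary; three to five are predicted in the intervention arm against a cited mean of eight for physiotherapy, and some participants may not return at all. The arms have different physiotherapists, none of them blinded. This stands, and it shapes the fix.

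**Conclusion.** The point holds in this form: under the Monitoring rule, adverse events cannot be counted, compared between arms or reported. The stated expectation of none cannot be tested, and the tolerability aim rests on form completeness and a handful of interviews. Nothing in the document shows that the exercise is unsafe, and no change to the exercise follows from this point.

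What is forgone is modest but real. With full reporting, zero events in an arm of 30 would give a two-sided 95% upper limit of 11.6%; at the plan's own 75% completeness threshold the limit is about 15%. These figures assume 30 participants per arm and independent participants, and the second also assumes that those who report are like those who do not. With numbers this small, any comparison between arms would be descriptive only.

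**What to change.** Replace the Monitoring statement with a commitment to collect adverse events in the same way in both arms. Add a short structured item to the 3- and 6-month postal questionnaires covering new injury, a fall, and a flare that led to stopping exercise or seeking healthcare. Report counts and proportions by arm with exact confidence intervals and the number of participants who answered. In Planned data analysis, add these results to the assessment of tolerability, beside the interviews.

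If physiotherapists also note events at sessions, treat that record as supplementary and do not use it to compare arms, because frequency of contact may differ between them.

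The cost is a few extra lines on forms already sent to both arms, and a protocol amendment. The postal item needs no new participant contacts.

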### Patient and public involvement

This research project has been driven by the views of people suffering from patellofemoral pain (PFP). Patients who receive physiotherapy for PFP have been consulted for their views, including patient members of the Steering Group Committee. Thoughts and preferences to current programmes of therapy and treatment have been requested, and these views have been incorporated into the planning, design, application and dissemination of this study.

Patients stressed the importance of ensuring minimal number of exercises for improved adherence; the tailoring of the physiotherapy intervention around their usual sport/hobbies (where appropriate); and the capability of telephone support when required at short notice.

The main exercise of the intervention itself was adapted after consultation with patients. Initially, the intervention was an exercise based upon the ‘Step Down’ function test [47]. The feedback from the patients was that performing the same manoeuvre sideways, rather than facing down the step, allowed them to use the guide of the wall and/or banister with their hands. This has been incorporated into the intervention.

## Discussion

We have presented the rationale and design of a mixed-methods feasibility study for a loaded self-managed exercise programme for PFP. The premise that a loaded self-managed lower limb strengthening exercise, that is not directed at specific tissue pathology, but rather based on the neurophysiology of pain, set within clearly defined boundaries, will have a positive impact upon fear-avoidance, catastrophizing and self-efficacy behaviour and patient-reported pain levels. The feasibility of a large definitive RCT will either be established or negated, and the results of the trial will be published when they are available.

## Abbreviations

CKRS: Cincinnati knee rating system
CSP: Chartered Society of Physiotherapy, UK
EQ-5D-5L: Euro-QOL
GSES: General self-efficacy scale
HEE: Health Education England
MCID: Minimal clinically important difference
MRI: Magnetic Resonance Imaging
MSK: Musculoskeletal
NHS: National Health Service
NIHR: National Institute for Health Research
PCS: Pain catastrophizing scale
PFP: Patellofemoral pain
RCT: Randomised controlled trial
TSK: Tampa Scale for Kinesiophobia
VAS: Visual analogue scale
